**Methods and analysis::**

Participants will be randomized 1:1 in intervention (PKNS) and control (standard-of-care) arms. Assessments will be undertaken at baseline and after 6 and 12 months. Primary outcome measure is the Parkinson’s Disease Questionnaire 39-items scale total score. Secondary measures include the clinical scales testing motor and non-motor symptoms, caregiver burden, adherence to therapy, cumulative disease burden and the number of unplanned hospital visits/admissions during the study period. The cost-effectiveness of this method will be evaluated by using the EuroQoL-5, which estimates the incremental cost per quality-adjusted life-years gain. Real-life motor autonomy will be objectively measured by collecting waist-worn wearable data on gait parameters (automatically detecting motor patterns indicative of freezing of gait and falls) in all subjects for five consecutive days each month during the 12-month duration of the study.

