**Figure 1. fig1-17562864241299347:**
[figure not shown]
Study design. *Blood Pressure (BP) and Heart Rate (HR) are measured in the supine position and after 3 min of active standing. ADL, Activities of Daily Living; CFS, Clinical Frailty Scale; CIRS, Cumulative Disease Rating Scale for Geriatrics; EQ-5D-5L, European Quality of Life 5 dimensions; FOG-Q, Freezing of Gait Questionnaire; H&Y, Hoehn and Yahr; IADL, Instrumental Activities of Daily Living; MDS-UPDRS, Movement Disorder Society-sponsored revision of the Unified Parkinson’s Disease Rating Scale; MMAS, Morisky Medical Adherence scale-8 items; MSA, Multiple System Atrophy; NMSS, Non-Motor Symptoms Scale; PDQ-39, Parkinson’s Disease Questionnaire-39; PSP, Progressive Supranuclear Palsy; PSPRS, Progressive Supranuclear Palsy Rating Scale; UMSAR, Unified Multiple System Atrophy Rating Scale; ZBI, Zarit Burden Interview scale.

At baseline (V1) and 12 months (V5), the blind rater will collect: demographic and social information (including caregiver’s relationship with the patient (e.g., spouses, siblings, hired caregivers, etc.) and the number of caregivers per patient), general and neurological examination; PD Questionnaire-39 (PDQ-39);^
20
^ Movement Disorder Society-sponsored revision of the Unified PD Rating Scale (MDS-UPDRS);^
21
^ Hoehn and Yahr stage (H&Y); Freezing of Gait Questionnaire (FOG-Q);^
22
^ Unified MSA Rating Scale (UMSARS) in patients diagnosed with MSA or PSP Rating Scale (PSPRS) in patients diagnosed with PSP;^23,24^ Non-Motor Symptoms Scale (NMSS);^
25
^ Activities of Daily Living (ADL, IADL);^26,27^ Zarit Burden Interview scale (ZBI);^
28
^ European Quality of Life 5 dimensions (EuroQoL);^
29
^ Cumulative Disease Rating Scale for Geriatrics;^
30
^ Morisky Medical Adherence scale-8 items (MMAS-8).^
31
^ All patients and care providers will be trained on using the wearable sensor and its free downloadable app on their smartphones at the screening assessment and, to confirm understanding, at the baseline visit. At follow-up after 6 months (V3), the blind rater will perform a neurological examination, record any incident medical events (including falls) and hospitalizations, and collect PDQ-39.

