#### Secondary outcomes

1. To evaluate the feasibility and effectiveness of an innovative telenursing approach consisting of proactive and reactive remote monitoring aimed at optimizing continuity of care by improving motor and non-motor disability control, including through better adherence (compliance) to the prescribing regimen. Outcome measures will be the changes in MDS-UPDRS (Parts I, II, and III) and NMSS scores in all participants. Disease-specific scales will also be used: (a) UMSARS in subjects diagnosed with MSA and (b) PSPRS in those diagnosed with PSP. In addition, changes in scores on the functional disability (CFS) and autonomy in activities of daily living (IADL, ADL) scales will be used. Compliance to prescribing regimen will be measured by the changes in scores on the Italian version of the MMAS-8 on adherence to pharmacological therapy.^
31
^2. To investigate the cost-effectiveness of the management model by telenursing compared to standard care in terms of (a) reducing the number of unplanned hospital admissions and (b) reducing complications/comorbidities to minimize direct and indirect costs to the national healthcare system. We will analyze differences between the two study groups in the number of unplanned hospital admissions in 12 months through an interview to patient and/or care provider (calculating outpatient visits, emergency room admissions, hospitalizations directly or indirectly associated with neurological pathology). In addition, differences between the two study groups in comorbidity frequency (total events, disease-related events) through (a) patient and/or caregiver interview and (b) the Italian version of the Cumulative Illness Rating Scale for Geriatrics^
30
^ will be evaluated. To estimate the incremental cost per quality-adjusted life-year gain (QALY)^
29

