^ change from baseline to 12 months of the EuroQoL scale total score will be analyzed.3. To evaluate the feasibility and utility of telemonitoring to improve PKNS and neurologist decision-making using a device worn at the waist for 5 days per month (8 h/day), which passively collects data on real-life motor autonomy and fall risk, including FOG episodes. Changes in gait parameters in both between-group (between-group) and same-patient (within-group) analyses will be evaluated to obtain information on changes in physical activity, motor autonomy, gait disorders (including FOG), and risk of falls.4. To reduce the risk of caregiver burnout. Changes in the ZBI on caregiver burnout^
28
^ from baseline to 12-month follow-up will be used.5. Patient satisfaction by evaluating the differences to the patient satisfaction questionnaire.

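### The measure named for cost per QALY, the 12-month change in a EuroQoL total score, is not a QALY; even on a utility scale it would overstate QALYs gained twofold

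*Protocol article*

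**What the plan says.** Cost-effectiveness stands beside efficacy in the Objectives of the abstract. The abstract's Methods and analysis paragraph says: "The cost-effectiveness of this method will be evaluated by using the EuroQoL-5, which estimates the incremental cost per quality-adjusted life-years gain".

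Secondary outcomes, item 2, gives the aim and the measure in one sentence. It opens "To estimate the incremental cost per quality-adjusted life-year gain (QALY" and closes by saying that the "change from baseline to 12 months of the EuroQoL scale total score will be analyzed".

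The legend of Figure 1 identifies the instrument: "EQ-5D-5L, European Quality of Life 5 dimensions". On timing, the Clinical assessment section introduces the battery that contains the EuroQoL with "At baseline (V1) and 12 months (V5), the blind rater will collect". For the 6-month visit (V3), the same section lists a neurological examination and says that the rater will "record any incident medical events (including falls) and hospitalizations, and collect PDQ-39". PDQ-39 is the only questionnaire named there.

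The article does not mention a utility index, integration over time, or how deaths enter the QALY calculation.

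**The concern.** The article goes further than leaving the health-economic method open. It names a target (cost per QALY), an instrument (EuroQoL) and a contrast (baseline-to-12-month change in total score), and the contrast does not produce the target. QALYs need two steps that the sentence omits: preference weights that turn a health profile into a utility, and accumulation of that utility over the year. A change score compares the two ends of the year and says nothing about how much health was experienced between them.

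The Rationale says that the results are meant to support proposing the care model to stakeholders. If an analyst divided incremental cost by the difference in change, the denominator would be too large and the cost per QALY too low. For an intervention that works and costs more, that error flatters the intervention.

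**Working it through.** **Inputs.** The documents give the horizon (12 months, from Study design) and the EuroQoL time points (V1 and V5, from Clinical assessment). They state no utility, cost, QALY or mortality figure, so there is no plan figure to reproduce; the sample size concerns PDQ-39 and has no bearing here. All utilities and death rates below are assumptions for illustration.

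**Step 1. Change against QALY, reading total score as the utility index.** Write u0 for baseline utility, and uC and uT for 12-month utility in the control and intervention arms. Over one year, with a straight-line path:

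- QALY per arm = (u0 + u12)/2
- Between-arm QALY difference, equal baselines = (u0 + uT)/2 − (u0 + uC)/2 = (uT − uC)/2
- Between-arm difference in change = (uT − u0) − (uC − u0) = uT − uC

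The ratio is 2, whatever the utilities.

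**Step 2. Numbers put in.** Assume u0 = 0.50, uC = 0.35, uT = 0.40.

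- Difference in change: −0.10 − (−0.15) = 0.05
- QALYs: (0.50 + 0.40)/2 = 0.450 and (0.50 + 0.35)/2 = 0.425, difference 0.025
- Cost per QALY for each 1,000 of incremental cost: 1,000/0.05 = 20,000 with the change, 1,000/0.025 = 40,000 with QALYs

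If total score is instead an unweighted sum over the five dimensions, it is not on a QALY scale and no such conversion applies.

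**Step 3. Deaths.** A patient who dies before V5 has no 12-month score and therefore no change. Keep the Step 2 utilities for survivors and assume that a patient who dies falls in a straight line from 0.50 to 0 at 6 months, accruing 0.50 × 0.5/2 = 0.125 QALY. The all-patient mean per arm is (1 − d) × survivor QALY + d × 0.125, where d is the proportion who die.

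| Assumed deaths, control / intervention | Intervention mean | Control mean | QALY difference |
|---|---|---|---|
| Survivors only | 0.45000 | 0.42500 | 0.025 |
| 5% / 5% | 0.43375 | 0.41000 | 0.024 |
| 10% / 5% | 0.43375 | 0.39500 | 0.039 |
| 15% / 10% | 0.41750 | 0.38000 | 0.0375 |
| 20% / 10% | 0.41750 | 0.36500 | 0.0525 |

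Equal mortality hardly matters. Unequal mortality can matter as much as the utility effect itself.

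**Step 4. What a 6-month value would add.** With a value at V3, QALY = (u0 + 2·u6 + u12)/4. Keeping the Step 2 endpoints:

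- u6 = 0.425 control, 0.45 intervention (on the straight line): (2 × 0.025 + 0.05)/4 = 0.025
- u6 = 0.40 and 0.47: (2 × 0.07 + 0.05)/4 = 0.0475
- u6 = 0.45 and 0.45: (0 + 0.05)/4 = 0.0125

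Two points give an answer, but it depends on the straight-line assumption.

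**The case against.** The strongest reply is that total score is loose wording. The article also calls its primary outcome the PDQ-39 total score while noting that a summary index exists. The EQ-5D-5L can be converted to utilities, and the sentence says that the change will be analysed, not that it is the denominator of the cost-effectiveness ratio. The full protocol, SAP or a health-economic plan may set this out properly. This is fair as to intent, and it is why no claim is made that the final analysis will be wrong. It does not rescue the sentence: the only measure tied to cost per QALY is a change score, and Step 1 shows that even the charitable reading is wrong by a factor of two.

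A reader might also infer three stronger things, which the article does not support:

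- **That two measurements cannot yield QALYs.** They can, by linear interpolation, as Step 1 does. A missing 6-month value makes the estimate cruder, not invalid. That the EuroQoL is collected only twice also rests on the text alone, since the schedule in Figure 1 is not shown.
- **That patients who die will be excluded.** No section says so. It follows only if the change score is used literally. The Safety section collects all serious adverse events, so deaths should be on record and can be counted.
- **That the sensor's cost will cancel between arms because everyone wears it.** The article gives no costing rule, so nothing can be concluded.

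Naming the value set and the method for confidence intervals is detail that a condensed article may leave to the SAP.

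**Conclusion.** The point holds as a wrongly stated measure. A change in EuroQoL total score does not give QALYs. If it is a utility index and is used as QALYs gained, the denominator is doubled and the cost per QALY halved. That factor rests on equal baselines, straight-line paths and a one-year horizon, not on the utilities chosen. Taken literally, the measure also leaves out QALYs lost to death. In the assumed scenarios, counting deaths moved the between-arm difference from 0.025 to between about 0.024 and 0.053. Those figures show possible size only, since the article gives no mortality rate, although its Background acknowledges raised mortality risk as disease progresses.

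Severity is moderate. This is part of a secondary outcome; the PDQ-39 primary outcome, its sample size and its test are unaffected, and the repair can be made from data already planned.

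**What to change.** Replace the sentence in Secondary outcomes, item 2, with wording to this effect: EQ-5D-5L profiles will be converted to utilities; each patient's 12-month QALYs will be the area under the utility curve by the trapezoid rule, with utility 0 from the date of death; arms will be compared with adjustment for baseline utility. Baseline adjustment matters because a chance imbalance in u0 carries directly into the area. The abstract should say that the EuroQoL supplies the QALY side of the ratio, not that it estimates the ratio. This costs only wording, settled before database lock, and needs no new data.

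Optional: add the EQ-5D-5L at V3, where PDQ-39 is already collected, for patients not yet past that visit. This costs a few minutes per patient and a minor amendment at four sites, and patients already past V3 keep two-point data. Recruitment began in August 2023 with completion planned for November 2024, so the gain shrinks with delay. If it is added, apply the same interpolation rule in both arms and report the two-point result for all patients alongside.

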### Safety

All adverse events (AEs) including all Serious adverse events will be collected, properly investigated, and documented in the original documents and appropriate sections of the eCRF during the entire study period, from the signing of informed consent to the last protocol-specific procedure, including the follow-up period for safety.

### Analysis plan

#### Simple size

This is the first study to investigate the efficacy of an integrated program in patients with rare forms of parkinsonism such as MSA and PSP, whereas this has been previously studied only in PD.^
4
^ Considering that there is no validated questionnaire measuring quality of life in MSA and/or PSP, we relied on data from a previous randomized trial on the effectiveness in terms of health-related quality of life of an integrated program coordinated by a case manager versus the standard of care in PD.^
4
^ We hypothesized a difference of at least 3, 9 in change at 12 months in the PDQ-39 between the proposed integrated care model and the standard of care, with expected standard deviations of 8.6 in the control group and 5.8 in the treated group. Considering a type I error of the two-tailed *t*-test of 5%, a power of 90% and a loss to follow-up of no more than 10%, a sample size of 164 patients (82 per arm) is needed. Although patients with MSA and PSP are expected to show a more aggressive disease course than PD with a more rapidly worsening course of disability and quality of life than idiopathic PD, we decided to maintain a similar effect size to compensate for the potential lower specificity of the primary outcome measure (e.g., PDQ-39).

#### Statistical analysis

No intermediate analysis is planned. The primary analysis will be by intention to treat principle as far as is practically possible. Analysis by protocol (PP) will be done after excluding patients with major deviations from the protocol. Descriptive statistics by treatment arm will be provided for all variables assessed in the study protocol with mean and standard deviation and median with range for continuous variables and absolute numbers and percentages for categorical variables.

The primary analysis will be based on the two-tailed *t*-test. Changes from baseline in the primary and secondary continuous variables (including longitudinal data obtained from the wearable device) will be analyzed by analysis of variance for repeated measures adjusted for baseline, or a corresponding nonparametric analysis as appropriate. Safety analysis will be performed by calculating the proportion of patients with AEs. The *p* values < 0.05 will be considered statistically significant, and all tests will be two-sided. The STATA Statistical Software, Release 16 (StataCorp. 2019. Stata Statistical Software: Release 16. College Station, TX: StataCorp LLC) will be used for statistical analysis.

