### Outcome measurements

#### Primary outcome

The primary aim is to demonstrate that an integrated care delivery model coordinated by a PKNS results in more favorable changes in quality of life at 12 months than standard medical care. The outcome measure will be the change from baseline to 12-month result in PDQ-39 total score, comparing cases to controls. PDQ-39 scale is a comprehensive assessment battery composed of 39 items grouped into eight subscales (mobility, activities of daily living, emotional well-being, stigma, social support, Cognition, Communication, and Bodily discomfort). Each item scores from 0 (never) to 4 (always); subscale scores and a summary index representing the global health-related quality of life can be obtained. PDQ-39 does not present any relevant ceiling or floor effect and has been demonstrated to be consistent, reliable, and discriminative for disease severity.^
35
^

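### Of two methods named for PDQ-39 change, the article makes primary the t-test, which cannot use the 6-month PDQ-39, baseline adjustment or the stratification factors

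*Protocol article*

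**What the plan says.** All references are to the protocol article.

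- **Endpoint** (Primary outcome): "The outcome measure will be the change from baseline to 12-month result in PDQ-39 total score, comparing cases to controls".
- **Population** (Statistical analysis): "The primary analysis will be by intention to treat principle as far as is practically possible". A per-protocol analysis follows.
- **Methods** (Statistical analysis): the primary analysis is a two-tailed t-test. The next sentence assigns changes from baseline in both primary and secondary continuous variables to a repeated-measures analysis of variance adjusted for baseline, or a nonparametric counterpart. PDQ-39 change therefore has two named methods, and the t-test is the one called primary.
- **6-month data** (Clinical assessment): at V3 the blind rater will "record any incident medical events (including falls) and hospitalizations, and collect PDQ-39".
- **Stratification** (Randomization and blinding): sex, diagnosis (MSA or PSP), and Clinical Frailty Scale up to 4 versus above 4.
- **Sample size** (section headed Simple size): "We hypothesized a difference of at least 3, 9 in change at 12 months in the PDQ-39", with "expected standard deviations of 8.6 in the control group and 5.8 in the treated group", a "type I error of the two-tailed *t*-test of 5"%, 90% power and "a loss to follow-up of no more than 10"%, giving 82 per arm. The same paragraph begins its caveat with "Although patients with MSA and PSP are expected to show a more aggressive disease course than PD".

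**The concern.** A two-sample t-test on change from V1 to V5 needs a V5 value for each patient. It has no place for V3. Baseline enters only by subtraction, not as a covariate, and the three stratification factors do not enter at all. A patient who gives a PDQ-39 at 6 months and is then lost contributes nothing unless a value is imputed.

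This matters if loss is related to outcome, and the article gives reasons to expect that. It describes a faster course than Parkinson's disease, says that complications raise mortality, and requires in-person assessment at V5. The intervention is meant to prevent falls, complications and admissions, so it could also change who reaches V5. The t-test would then compare two selected groups, although a measurement that helps to correct for the selection has already been taken at V3.

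**Working it through.** **1. The plan's own figure.** Inputs from the sample-size section: difference 3.9, SDs 8.6 and 5.8, two-sided alpha 0.05, power 0.90, loss 10%.

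n per arm = (8.6² + 5.8²)(1.960 + 1.282)² / 3.9² = (73.96 + 33.64) × 10.51 / 15.21 = 74.33.

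Allowing for loss: 74.33 × 1.1 = 81.8, or 82 per arm (164), as stated. Dividing by 0.9 instead gives 82.6, or 83 per arm (166). Rounding to 75 first gives 84 per arm (168). The stated 164 is reproduced, and it corresponds to about 74 observed V5 values per arm.

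**2. Power of the t-test on observed V5 values.** Noncentrality = 3.9 / √(107.60 / n), with n = 82 × (1 − loss).

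| Loss | n per arm | Noncentrality | Power (noncentral t) | Power (normal approx.) |
|---|---|---|---|---|
| 10% (planned) | 73.8 | 3.23 | 0.894 | 0.898 |
| 20% (assumed) | 65.6 | 3.05 | 0.856 | 0.861 |
| 30% (assumed) | 57.4 | 2.85 | 0.806 | 0.813 |

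The planned loss costs nothing beyond what the design allows for. Higher losses cost moderate power.

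**3. Bias, simple form.** Suppose lost patients worsen by D points more than observed patients, with the same D in both arms. Then the observed-V5 difference minus the all-randomised difference = −(loss in control − loss in intervention) × D.

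- 20% control, 10% intervention, D = 5 to 10: −0.5 to −1.0 points (0.5/3.9 = 13% to 1.0/3.9 = 26% of the target).
- 10% control, 20% intervention: +0.5 to +1.0 points.
- Equal loss: zero.

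The size and the sign both depend on the assumed pattern.

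**4. Bias when loss follows 6-month change.** This is a simulation. Mean worsening at 6 and 12 months is 2 and 3.9 in control, and 0 and 0 in intervention. The 12-month SDs are 8.6 and 5.8, and the 6-month SDs are 0.8 times those. The correlation between 6- and 12-month change is 0.6. Loss after V3 is logistic in the 6-month change. Apart from the 3.9 and the two SDs, these are assumptions. The V3 column regresses 12-month on 6-month change within each arm and fills in the missing values. All differences are control minus intervention.

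| Intercept, slope per point | Loss, control / intervention | Observed V5 only | Using V3 |
|---|---|---|---|
| −2.3, 0 | 9% / 9% | 3.87 (true 3.87) | 3.87 |
| −2.3, 0.1 | 13% / 10% | 3.63 | 3.90 |
| −1.6, 0.1 | 22% / 18% | 3.44 | 3.89 |
| −1.2, 0.1 | 29% / 24% | 3.33 | 3.90 |
| −1.6, 0.2 | 29% / 20% | 2.93 | 3.91 |

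A second run of the same kind fixed the loss rates directly. It gave 3.62 (10%/10%), 3.42 (20%/20%), 3.21 (20%/10%) and 3.01 (30%/20%), with 3.86 to 3.91 recovered through V3. Equal loss still biases the result here because mean worsening and spread differ between the arms, so the simple formula in step 3 does not cover this case.

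The first row shows that loss unrelated to outcome produces no bias. V3 recovers the truth so fully because loss was made to depend only on V3. Loss that also depends on unseen later decline would be corrected only in part.

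**The case against.** The strongest reply is that the article is a condensed account and less is wrong than may appear. Four parts of it stand.

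- A reader might infer that the primary analysis is restricted to survivors who complete V5. No such rule is written. A t-test on imputed changes would also fit the text, and rules for missing data and death may sit in the full protocol or SAP. Their absence here is no finding.
- A reader might infer that intention to treat is abandoned. The statement is openly qualified, 10% loss is budgeted, and power at that loss is close to the planned 90%.
- A reader might infer that the 6-month PDQ-39 goes unused. It does not: the baseline-adjusted repeated-measures analysis covers the primary variable and can take in V3. Nor can that analysis be dismissed as needing complete data for every patient, because the article does not say how it will be fitted.
- The article gives no mortality or dropout rate beyond 10%. It excludes Hoehn and Yahr stage 5, Clinical Frailty Scale 8 or above, and dementia at entry, which removes some of the patients most likely to become unassessable.

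What the reply does not answer is the ranking of the two methods. The choice of the t-test as primary is stated in the article, not left to another document. The qualifier in the intention-to-treat sentence does not justify it either, because a practicable method that can use more of the randomised patients' data is named in the next sentence.

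**Conclusion.** The point holds as a poor choice of primary method. The article ranks a t-test that cannot use V3, baseline adjustment or the stratification factors above a repeated-measures method that can use V3 and adjusts for baseline. Without imputation the t-test rests on patients with a V5 score, which undermines the qualified intention-to-treat aim but does not contradict it outright.

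The size is conditional. At the planned 10% loss, power is about 0.89 and nothing is lost against the design. If loss reaches 10-30% and follows 6-month worsening, with a correlation of 0.6, the observed-V5 difference is roughly 3.0 to 3.6 points (lowest case 2.93) instead of 3.9, and using V3 removes most of the gap. These loss rates, the correlation and the mechanism are assumptions. In the simulated cases the bias runs against the intervention, but heavier loss in the intervention arm could reverse it (step 3). The gain in precision from adjusting for baseline and strata cannot be quantified, because the article gives no correlations.

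**What to change.** Name one primary analysis: a likelihood-based mixed model for repeated measures on PDQ-39 at V3 and V5, with arm by visit, baseline by visit, sex, diagnosis and frailty stratum. Use an unstructured covariance, preferably separate by arm because the planned SDs differ. The arm contrast at V5 is the primary estimate. Keep the t-test as supportive.

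The model has limits that should be stated. It assumes missing at random, leaves out patients with no follow-up PDQ-39, and implicitly estimates scores after death. So add two sensitivity analyses:

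- one for loss that is not at random, such as delta-adjusted imputation;
- one that treats death separately, for example a stratified rank test with deaths ranked worst.

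The cost is small. V3 is already scheduled, standard Stata commands suffice, and 82 per arm can stand. No interim analysis is planned, so the change can be documented before outcomes are seen by arm. The downside is a model-based estimate that is less simple to explain than a t-test, and a little more analysis work. If the SAP already specifies such a model, only the wording of the primary analysis needs to be aligned.

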### Randomization and blinding

Eligible patients will be randomized with 1:1 allocation into the two treatment arms with a centralized web-based randomization system. The randomization list will be generated by computer. Randomization is stratified by (1) sex, (2) diagnosis (MSA vs PSP), and (3) disability (CFS ⩽ 4 vs. > 4). For blinding purposes, the CRC schedules evaluation by a blind neurologist (“blind rater”) of all enrolled patients, blind to randomization. The blind rater will perform the scales and questionnaires prescribed in the protocol. The patient knows if he/she will follow the “case-manager” procedure or if he/she will be approached with the standard-of-care model.

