### Intervention and monitoring

#### Intervention arm

Patients in the intervention arm will receive care from a PKNS for any medical (non-administrative) needs tailored to their necessities and standard medical treatment. A PKNS from each site will follow the patients enrolled.

- *PROACTIVE monitoring*: At baseline (V1), the PKNS contacts the patient to create a personal record using a semi-structured interview, including all symptoms of motor and non-motor characteristics and the type of risks that may occur. The PKNS instructs on risk prevention strategies related to the most relevant issues reported. After the initial proactive call to V1, PKNS will provide intermediate contacts every 3 months. At intermediate calls (V2, V3, V4), the PKNS focuses the interview on the problems/risks detected at baseline and provides tailored counseling and education. At the final visit (V5), the investigator will complete the follow-up of all the incident events and medical issues occurred during the study.- *REACTIVE monitoring*: During the study period, the patient and care provider may contact the PKNS at any time prior to the previously scheduled in-person visit for urgent needs by telephone (3h/day, 5 days/week, Mon-Fri) or by e-mail (within 48 h).

The PKNS can (1) also address the specific problem by interacting with the participant’s primary care physician and other healthcare providers or (2) refer to the treating neurologist (who is not the blind rater) for teleconsultation or in-person visit, according to a semi-structured algorithm that assigns four levels of priority similar to emergency room “triage”.^
19
^ Briefly, whenever a referral to a neurologist is needed, PKNS assigns a 4-level code triage, where increased urgency would lead to reduced assessment time and the opportunity for a teleconsultation with an experienced neurologist. We proposed this approach to triage patients query during COVID-19 pandemic, including a detailed flowchart.^
19

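### The primary analysis of PDQ-39 is an unadjusted t-test, and the next sentence gives the same variable a baseline-adjusted ANOVA or a nonparametric test with no ranking

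*Protocol article*

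**What the plan says.** The Primary outcome section fixes the endpoint: "The outcome measure will be the change from baseline to 12-month result in PDQ-39 total score, comparing cases to controls".

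Two adjacent sentences in the Statistical analysis section then deal with it. The first reads "The primary analysis will be based on the two-tailed" t-test. The second begins "Changes from baseline in the primary and secondary continuous variables (including longitudinal data obtained from the wearable device) will be analyzed by analysis of variance". It goes on to make this a repeated-measures model with baseline adjustment and leaves a nonparametric counterpart open. The second sentence names the primary variable explicitly. It does not call its analysis supportive, secondary or a sensitivity analysis, and it does not say what would trigger the nonparametric option. One rule covers everything: p "values < 0.05 will be considered statistically significant, and all tests will be two-sided".

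The Randomization and blinding section states "Randomization is stratified by (1) sex, (2) diagnosis (MSA vs PSP), and (3) disability", the last being the Clinical Frailty Scale (CFS) split at 4. The sample size section rests on a two-tailed t-test. PDQ-39 is collected at baseline, 6 months and 12 months (Clinical assessment).

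**The concern.** There are two linked problems.

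First, the named primary test leaves information unused. A two-sample t-test on change cannot take baseline PDQ-39 as a covariate, nor the three factors on which the randomisation is balanced. Balancing on prognostic factors and then leaving them out of the analysis makes the standard error too large for the design. The test is then conservative, and precision already paid for in the data collection is lost.

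Second, the ANOVA and its nonparametric alternative cover the same variable without a rank. The t-test and a baseline-adjusted model are different estimators and can fall on opposite sides of 0.05. A repeated-measures ANOVA could also bring in the 6-month visit and test a contrast other than the 12-month change. If the results disagree, the text does not say that the second analysis is only supportive. A choice of emphasis made after the data are seen would be hard to defend on the endpoint that decides the trial.

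**Working it through.** **Inputs from the sample size section.** Difference 3.9 points; SD of change 8.6 (control) and 5.8 (intervention); two-sided alpha 5%; power 90%; loss to follow-up 10%; 82 per arm.

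**Inputs that are assumptions.** The document gives neither the baseline to 12-month correlation r nor the share R² of the variance in change that the strata explain. Ranges used: r = 0.5 to 0.8 for power, r = 0.4 to 0.8 for type I error, and R² = 5% to 20%.

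**1. The plan's own figure.**
- Average SD = √((8.6² + 5.8²)/2) = √((73.96 + 33.64)/2) = 7.335.
- n per arm = 2 × (7.335 × (1.960 + 1.282)/3.9)² = 74.3.
- 74.3 × 1.10 = 81.8, so 82 per arm and 164 in total. Rounding up to 75 and dividing by 0.90 gives 84 per arm (168).

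The stated 164 therefore reproduces, and it belongs to the unadjusted t-test.

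**2. Power of the t-test.**
- Evaluable per arm = 82 × 0.90 = 73.8.
- SE = √((73.96 + 33.64)/73.8) = 1.207.
- 3.9/1.207 = 3.23, which gives 89.4% power from the t distribution.

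**3. Gain from baseline adjustment.** With equal variance σ² at both visits, the change score has variance 2σ²(1 − r), and the 12-month score adjusted for baseline has variance σ²(1 − r²). The ratio is (1 + r)/2.

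| r | variance ratio | SE | power |
|---|---|---|---|
| none (t-test) | 1.00 | 1.207 | 89.4% |
| 0.5 | 0.75 | 1.046 | 96% |
| 0.6 | 0.80 | 1.080 | 95% |
| 0.7 | 0.85 | 1.113 | 94% |
| 0.8 | 0.90 | 1.146 | 92% |

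**4. Strata left out.** If the strata are balanced by design and explain a share R² of the variance, the true variance of the difference is (1 − R²) times what the t-test assumes. True alpha = 2 × (1 − Φ(1.96/√(1 − R²))).

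| R² | 1.96/√(1 − R²) | true alpha |
|---|---|---|
| 5% | 2.011 | 4.4% |
| 10% | 2.066 | 3.9% |
| 15% | 2.126 | 3.4% |
| 20% | 2.191 | 2.8% |

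**5. Cost if either analysis could count.** Under the null, the t statistic on change and the 12-month ANCOVA statistic have correlation √((1 + r)/2). The bivariate normal probability that at least one exceeds 1.96 in absolute value is:

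| r | correlation of the statistics | chance of at least one p < 0.05 |
|---|---|---|
| 0.4 | 0.837 | 7.6% |
| 0.5 | 0.866 | 7.3% |
| 0.7 | 0.922 | 6.8% |
| 0.8 | 0.949 | 6.5% |

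**The case against.** The strongest reply is that the plan does name one primary analysis. Only the t-test carries that label, the Primary outcome section defines the matching 12-month change, and the sample size was built on the same test. The ANOVA then reads naturally as an extra longitudinal analysis that uses the 6-month PDQ-39 and the monthly wearable data. This largely stands. A reader might infer that the plan has two rival primary analyses; the text does not go that far. What remains is that the second sentence includes the primary variable and gives its analysis no rank.

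A reader might also infer that the t-test is invalid or the trial underpowered. Neither follows. Under 1:1 randomisation the t-test is unbiased, any effect of leaving out the strata is conservative, and 164 matches the test named.

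It is also tempting to fault the ANOVA for omitting the strata, and both analyses for omitting centre, since "A PKNS from each site will follow the patients enrolled". The article is merely silent on the ANOVA's covariates, and a statistical analysis plan not shown here may supply them. Nothing in the document gives the centre question a size. Neither belongs to this point. The strata matter here only because a t-test cannot carry them.

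Finally, the power gains rest on a simple model. The ratio (1 + r)/2 with a common r and equal variances implies the same SD of change in both arms, while the plan expects 8.6 and 5.8. The gains are therefore indicative. Type I error above 7.6% can be produced by assuming that the ANOVA averages the 6- and 12-month visits or that the nonparametric test is also open, but the document does not specify that contrast.

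**Conclusion.** The point holds in a limited form. The primary analysis is valid and agrees with the sample size, but it is less efficient than a model using data the trial already collects, and the further analyses of the same variable are unranked.

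The size depends on assumptions: a gain of roughly 3 to 7 points of power (89.4% to 92% or 96%) for r between 0.8 and 0.5, and a true alpha between 4.4% and 2.8% if the strata explain 5% to 20% of the variance. The 6.5% to 7.6% type I error is conditional. It arises only if either result may be taken as positive, and it returns to 5% once the other analyses are declared supportive. This should be fixed before the data are seen; it is not a fatal flaw.

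**What to change.** Before database closure, replace the two sentences with one named primary analysis: an ANCOVA of PDQ-39 at 12 months with terms for arm, baseline PDQ-39, sex, diagnosis (MSA or PSP) and CFS stratum, reported as an adjusted mean difference with its 95% confidence interval. State that the t-test, the repeated-measures ANOVA and any nonparametric analysis of PDQ-39 are supportive and do not decide the primary conclusion.

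If the investigators prefer to keep the t-test as primary, labelling the rest supportive and stating when the nonparametric option applies would remove the ambiguity, but not the loss of precision.

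The cost is a short text change in the protocol or analysis plan. It needs no new data and does not affect patients. The sample size of 164 can stay, because under the assumptions above adjustment adds power.
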